**Methods:**

One hundred and eight men and women aged 18 to 65 years with mid-portion Achilles tendinopathy (who satisfy the inclusion and exclusion criteria) will be recruited. Participants will be randomised, using the website Sealed Envelope, to either a control group (sham heel lifts) or an experimental group (heel lifts). Both groups will be provided with education regarding acceptable pain levels to ensure all participants receive some form of treatment. The participants will be instructed to use their allocated intervention for at least 8 h every day for 12 weeks. The primary outcome measure will be pain intensity (numerical rating scale) at its worst over the previous week. The secondary outcome measures will be additional measures of Achilles tendon pain and disability, participant-perceived global ratings of change, function, level of physical activity and health-related quality of life. Data will be collected at baseline and the primary endpoint (week 12). Data will be analysed using the intention-to-treat principle. In addition, the acute kinetic and kinematic effects of the interventions will be examined at baseline in a subpopulation of the participants (*n* = 40) while walking and running using three-dimensional motion analysis.

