### Biomechanical assessment

At baseline, a subpopulation of participants who volunteer (*n* = 40) will undergo a biomechanical assessment to evaluate the acute changes in the biomechanical function of the Achilles tendon as this is the proposed mechanism of action of heel lifts. The variables of interest are Achilles tendon load (ATL), ankle joint moments and plantar/dorsiflexion range of motion (ROM), stance phase duration (SPD), ground reaction force (GRF) and tibial acceleration. One researcher (JB) will perform the assessment, with the support of experts in biomechanical analysis (ST, AG).

After completing a standardised and progressive 7-min warm-up, participants will be asked to walk (5 min) and run (3.5 min) with and without their allocated intervention (i.e. heel lift or sham heel lift) in four testing conditions: (i) walking, shoe only; (ii) walking with the allocated intervention; (iii) running, shoe only and (iv) running with the allocated intervention. The footwear used in testing will be standardised, using the same zero drop Merrell® shoe. The testing sequence will be randomised by a single author (JB). The gait conditions will be fixed at the participant’s optimal walking and preferred running speed to minimise the effect on biomechanical parameters [45].

Optimal walking speed (*V*) will be calculated to be a fourth of maximal walking speed, using the following calculation: *V* = sqrt(*L* × *g* × 0.25) [46]. The formula is based on the Froude number (0.25), leg length (*L*) and acceleration of gravity (*g*). Preferred running speed will be determined using a previously outlined method [47, 48]. Speed will be increased in increments of 0.1 km/h until they first report they have exceeded their preferred ‘comfortable’ running pace. Speed will then be decremented by 0.1 km/h until the participant has confirmed that their ‘comfortable’ running speed has been passed going down. This procedure will be repeated three times and speeds will be averaged to determine the preferred running speed. In between testing, participants will be given as long as required to recover and withdraw if pain exceeds 5 out of 10 on a VAS at any time during the trials [31].

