### Statistical analysis

Statistical analysis will be performed using the most recent version of SPSS (IBM Corp., Armonk, NY, USA) available at the time of analysis. Data will be double entered to minimise errors. Demographic data and anthropometric characteristics (e.g. gender, age, foot posture using the FPI, etc.) will be reported by the treatment arm.

The intention-to-treat principle will be used for all participants [61]. Multiple imputation will be used to replace missing data for the primary and secondary outcome measures [62], with the exception being ‘Global Rating of Change Scale, where no data substitution will be applied. Standard tests to assess continuous data for normal distribution will be used and transformation performed if required. The primary outcome measure assessed will be pain intensity (at its worst) at 12 weeks. Continuously scored outcome measures (pain intensity (NRS-11), VISA-A, LEFS, EuroQol 5—VAS, IPAQ-SF and biomechanical outcomes) will be analysed using an ANCOVA with adjustment for baseline scores [63].

Dichotomous data (Global Rating of Change Scale, adverse events and use of co-interventions) will be compared using relative risk, absolute risk increase and number needed to treat or harm. Intervention adherence and CEQ data will be compared between groups using independent *t*-tests. To complement point estimates, standard deviations, 95% confidence intervals and *p*-values will be calculated where appropriate.

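### The biomechanical ANCOVA leaves its baseline covariate unnamed and omits the randomised test order, which costs precision (not validity) in a 40-person sub-study

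*Protocol article*

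**What the plan says.** The Biomechanical assessment section of the protocol article describes a single session in 40 volunteers: "At baseline, a subpopulation of participants who volunteer" are tested, and no biomechanical follow-up is described. There are four conditions: "i) walking, shoe only; (ii) walking with the allocated intervention; (iii) running, shoe only and (iv) running with the allocated intervention". Participants are tested "with and without their allocated intervention (i.e. heel lift or sham heel lift", so allocation must be known before the insert conditions are run. On order, the section says only: "The testing sequence will be randomised by a single author". It does not say whether all four conditions are permuted or only shoe and insert within a gait, or whether the order is balanced.

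The Statistical analysis section then puts these outcomes in the same sentence as the 12-week questionnaires: the continuous outcomes "and biomechanical outcomes) will be analysed using an ANCOVA with adjustment for baseline scores". No other model term is named. What counts as the baseline score of a biomechanical outcome is not stated.

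**The concern.** An ANCOVA adjusted for baseline fits the questionnaires, which have a score before treatment and another at 12 weeks. It does not carry over unchanged to outcomes that are all recorded at baseline. The analyst has to decide what the covariate is, and the only value available to play that part is the shoe-only measurement in the same gait.

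That value has no fixed place in time. When the insert is tested first, the shoe-only value is recorded second, and any change over the session (settling to the treadmill, tiring, tendon pain) enters the covariate in some participants and the outcome in others. If order is not in the model, this variation goes into the residual.

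At stake is the precision of the analysis of the trial's stated secondary aim, in a sub-study for which the article gives no power calculation.

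**Working it through.** **The plan's own figures.** There is no calculation behind the 40 to reproduce. The total of 108 (99 plus dropout) concerns worst pain only. With f = 0.33 and one covariate, 99 participants give power 0.902, so the 99 is reproduced, and nothing below affects it.

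**How often shoe-only comes second.** If the four conditions are permuted freely there are 24 orders. Shoe-only follows the insert of the same gait in 12 of 24 (50%, about 20 of 40 participants), and in at least one gait in 18 of 24 (75%).

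**Model for the check.** 20 participants per arm; shoe-only value X and insert value Y each with SD 1 and correlation ρ; order random and independent of arm; whichever condition comes second is shifted by π (the order effect, in SD units); true arm effect on Y of 0.5. The values ρ = 0.8 and 0.9 and π = 0, 0.2 and 0.5 are assumptions, as the article gives none.

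**Closed form.** Let q = π²/4.
- Residual variance with order in the model: 1 − ρ².
- Residual variance without order: (1 + q) − (ρ − q)²/(1 + q).

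For ρ = 0.8, π = 0.2: q = 0.01, and 1.01 − 0.79²/1.01 = 0.392 against 0.36. The ratio of residual SDs is √1.089 = 1.044.

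For ρ = 0.9, π = 0.5: q = 0.0625, and 1.0625 − 0.8375²/1.0625 = 0.402 against 0.19. The ratio is √2.118 = 1.455.

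These ratios do not yet charge for the extra term.

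**Simulation with 40 participants** (60,000 runs per row, no carry-over). This includes the cost of the term.

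| ρ | π | SE without order | SE with order | Ratio | Closed form |
|---|---|---|---|---|---|
| 0.8 | 0 | 0.193 | 0.195 | 0.99 | 1.00 |
| 0.8 | 0.2 | 0.201 | 0.196 | 1.03 | 1.04 |
| 0.8 | 0.5 | 0.238 | 0.196 | 1.21 | 1.24 |
| 0.9 | 0 | 0.140 | 0.142 | 0.99 | 1.00 |
| 0.9 | 0.2 | 0.152 | 0.142 | 1.07 | 1.09 |
| 0.9 | 0.5 | 0.204 | 0.142 | 1.44 | 1.46 |

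(Ratios use unrounded standard errors; the 1.07 is 1.075.) In all six rows the mean estimate is 0.50 for a true 0.50, with or without order. Leaving order out therefore costs precision and introduces no bias.

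**Carry-over.** Suppose a fraction c of the insert effect persists into a shoe-only trial run afterwards. Half the participants are affected, and the ANCOVA slope is about ρ, so the contrast shrinks by about ρ × c/2. For c = 0.20 this is 0.8 × 0.10 = 8% to 0.9 × 0.10 = 9%. An order main effect does not remove it: at ρ = 0.8 and c = 0.50 the estimate is 0.40 with and without the term. A mixed model with a condition-by-arm contrast behaves, with complete data, like a change score with slope 1. It shrinks by c/2, giving 0.5 × (1 − 0.25) = 0.375, which is slightly worse.

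**Shoe-first subset.** Here the same-gait covariate precedes the insert. Under free permutation, the insert of the other gait still comes before it in 4 of these 12 orders, so the subset is not completely clean.

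**The case against.** The strongest reply is that this is a condensed article, and a sequence term in a sub-study model is the kind of detail left to a fuller document. For the order term alone, that has force: the article is silent on order and does not exclude it. It has less force for the covariate, because the article does fix a model, and that model points to a baseline score that these outcomes do not have in the ordinary sense.

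The design also has real safeguards: a standardised warm-up, fixed speeds, one standardised shoe, a randomised sequence and generous rest ("In between testing, participants will be given as long as required to recover and withdraw if pain exceeds 5 out of 10"). These make a large order effect less likely, so the 0.5 SD rows should be read as an upper scenario.

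Three stronger readings are tempting, and the documents do not support them.
- A reader might infer that chance imbalance in order between arms biases the result. Order is randomised independently of arm, so such imbalance is random error already reflected in the standard error. The randomisation method is not stated either, and balanced sequences would largely remove the imbalance.
- A reader might infer that the covariate is contaminated by treatment. This needs carry-over from a removable insert after unrestricted rest, and nothing in the article shows it. It cannot be excluded, but it remains an assumption.
- A reader might infer that participants who stop for pain are lost from the ANCOVA. The article does not say how incomplete sessions are analysed and gives no rate.

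**Conclusion.** The point holds as a minor one about clarity and efficiency. The stated ANCOVA names no usable baseline for outcomes measured only in the baseline session, and it omits the sequence that the trial randomises. The contrast between heel lift and sham stays unbiased. The loss is a standard error about 3 to 8% larger if the order effect is 0.2 SD, and about 21 to 44% larger if it is 0.5 SD; with no order effect, the extra term costs about 1%. These sizes rest on an assumed shoe/insert correlation of 0.8 to 0.9 and assumed order effects, and on reading shoe-only in the same gait as the covariate. Attenuation from carry-over (about 8 to 9% if 20% carries over) is hypothetical, and neither an order term nor a mixed model would cure it. The primary outcome and the sample size are unaffected.

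**What to change.** In the Statistical analysis section, give the biomechanical outcomes their own sentence. For each gait separately, the insert-condition value is analysed by ANCOVA with arm, the shoe-only value of the same gait, and test order (insert-first versus shoe-first).

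As a sensitivity analysis only, repeat the comparison in participants tested shoe-only first in that gait. With about 20 people its precision is low, so it serves to show whether the estimate moves in the direction carry-over would predict. It should not replace the main result.

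The cost is a few words and one degree of freedom. No new measurement is needed, provided the order actually used is recorded for each participant.

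The order term should be justified as a gain in precision, not as protection against carry-over.

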#### Secondary outcomes

The following secondary outcomes will be measured:Pain and disability (measured using the Victorian Institute of Sport Assessment—Achilles (VISA-A)) [39].Global Rating of Change Scale (measured using a 15-point Likert scale ranging from a ‘very great deal worse’ to a ‘very great deal better’). This variable will be dichotomized, with ‘effective’ defined as “somewhat better” or above [40];Function (measured using the Lower Extremity Functional Scale (LEFS) [41]);Health-related quality of life (measured using the VAS component of the EuroQol 5 Dimension 5 Level (EQ-5D-5L) questionnaire [42]);Level of physical activity (measured using the International Physical Activity Questionnaire—short form (IPAQ-SF) [43]).

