### Sample size

The sample size has been determined a priori using G*Power [55] based on pain intensity at its worst in the previous week as the primary outcome measure. We calculated the sample size using an *f*-test, analysis of covariance (ANCOVA). Using an allocation ratio of 1:1, 90% power, minimal clinically important difference of 1.5 units out of 10 [56], standard deviation of 2.3 [14], moderate effect size [57] (*f* = 0.33) and a significance level set at *a* < 0.05, we estimate that a total of 108 participants will be required (99 and an extra 9 for 10% drop-out) [58].

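### The Global Rating of Change responder comparison names no baseline covariate; adjusting for baseline pain and VISA-A is an optional, low-cost gain in precision

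*Protocol article*

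**What the plan says.** All of this is in the protocol article.

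- **Statistical analysis, continuous outcomes.** Worst pain (NRS), VISA-A, LEFS, the EuroQol VAS, IPAQ-SF and the biomechanical outcomes "will be analysed using an ANCOVA with adjustment for baseline scores". Adherence and treatment credibility/expectancy are also continuous but are compared by independent t-tests.
- **Statistical analysis, dichotomous outcomes.** Global Rating of Change, adverse events and co-intervention use "will be compared using relative risk, absolute risk increase and number needed to treat or harm". The sentence names effect measures only. It gives no model and no covariate, and it does not say that the comparison is unadjusted.
- **Secondary outcomes.** The Global Rating of Change is a 15-point scale. "This variable will be dichotomized" at a stated threshold.
- **Outcomes.** Primary and secondary outcomes are collected at baseline and week 12, so baseline pain and VISA-A will be available.
- **Randomisation and blinding.** Allocation is 1:1 in permuted blocks, with no stratification factor named.

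**The concern.** Adjustment is stated for the listed continuous outcomes and not for the responder outcome, so the responder result will most likely come from raw proportions. Baseline severity may well predict whether a participant reports improvement. If it does, leaving it out gives up precision that the data already in hand could supply.

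The trial is sized on pain, and no power is stated for the responder comparison. The risk difference and number needed to treat are nevertheless figures that clinicians will find easy to quote. What is at stake is the width of those intervals, not the direction or validity of the estimate.

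**Working it through.** **1. The plan's own sample size.** Inputs from Sample size: "Using an allocation ratio of 1:1, 90% power", "minimal clinically important difference of 1.5 units out of 10", "standard deviation of 2.3", f = 0.33, alpha 0.05.
- f = 1.5 / (2 × 2.3) = 0.326, rounded to 0.33.
- ANCOVA with two groups and one covariate, noncentral F with noncentrality N × f²: 99 × 0.33² = 10.78 gives power 90.2%. The stated 99 evaluable is reproduced.
- 108 × 0.9 = 97.2, so 98 evaluable (49 per arm) is used below.

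This figure concerns pain only, and adjusting the responder outcome would not change it.

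**2. Precision of the unadjusted comparison.** The document gives no responder rates. Assume 40% v 60%.
- SE of the risk difference = √(0.4 × 0.6/49 + 0.6 × 0.4/49) = 0.099.
- 95% half-width = 1.96 × 0.099 = 0.194, that is 19.4 percentage points.
- Power by formula is about 51%.

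**3. One baseline score, standardised logistic model.** 4,000 simulated trials per row, 40% v 60%. The strength of the score is assumed.

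| Odds ratio per SD of score | Variance ratio, crude/adjusted | Power, crude to adjusted |
|---|---|---|
| 1.0 | 0.99 | 53.6% to 53.2% |
| 1.25 | 1.00 | 53.1% to 53.3% |
| 1.5 | 1.04 | 52.1% to 53.5% |
| 2.0 | 1.09 | 52.1% to 55.8% |
| 3.0 | 1.23 | 52.5% to 60.6% |

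The mean risk difference is about 0.20 by both methods. With no true effect (40% v 40%), rejection rates were 5.6-5.9% crude and 5.6-5.8% adjusted.

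**4. Both scores, as proposed.** 98 evaluable, the two scores correlated 0.5 (assumed), each correlated r with the latent rating. Their joint R² is 2r²/(1 + 0.5). The repeat run used 6,000 trials per cell; its range covers 40% v 60% and 40% v 65%.

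| r | Joint R² | Variance ratio | Repeat run |
|---|---|---|---|
| 0 | 0 | about 0.98 | 0.97-0.98 |
| 0.1 | 0.013 | 0.98-0.99 | 0.99 |
| 0.2 | 0.053 | 1.01-1.02 | 1.01-1.03 |
| 0.3 | 0.120 | 1.06 | 1.05-1.06 |
| 0.4 | 0.213 | 1.13-1.14 | 1.10-1.11 |
| 0.5 | 0.333 | 1.23-1.28 | 1.22-1.24 |

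The mean risk difference was again the same by both methods.

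**5. In terms of the interval.** Dividing 19.4 points by the square root of the variance ratio gives 19.4/√0.98 = 19.6 points with useless scores, 19.4/√1.06 = 18.8 at r = 0.3, and 19.4/√1.28 = 17.1 at the most favourable value in the table.

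**The case against.** The strongest reply is that nothing is wrong. A relative risk, risk difference and number needed to treat from a randomised comparison are valid without adjustment, and the simulations confirm it: same mean effect, same false-positive rate. This stands in full.

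A reader might infer that the protocol is inconsistent because it adjusts one kind of outcome and not the other. The document does not support that. The baseline scores in the ANCOVA are most naturally each measure's own, and a rating of change has none. Nor is every continuous outcome adjusted, since adherence and credibility/expectancy are compared by t-tests.

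A reader might also infer that, without stratification, chance imbalance leaves the crude result unprotected. A particular imbalance can move a particular estimate, but the confidence interval already allows for this over repeated randomisation. What adjustment offers is a narrower interval, not the removal of bias.

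Two further replies carry weight. The unadjusted reading rests on silence: the sentence names effect measures that an adjusted model can also yield, and an analysis plan not shown here may set one. The gain also rests entirely on assumed correlations; with weak ones it is nil or slightly negative.

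What remains is that both scores are already collected, the likely reading is unadjusted, and the possible loss is small beside the possible gain.

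**Conclusion.** The point holds as an optional improvement on a secondary outcome. It is not an error, a bias or a contradiction, and the primary analysis and sample size are untouched.

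The expected change in the variance of the risk difference runs from a loss of about 2-3% if the scores are not prognostic, through a gain of roughly 1-6% at correlations of 0.2-0.3, to about 13-28% at 0.4-0.5 (10-24% in the repeat run). These figures assume 98 evaluable participants, the two scores correlated 0.5, and responder rates that the document does not state. It also gives no correlation between baseline severity and the rating, so where the trial would fall in this range is unknown.

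The figures apply to the Global Rating of Change only. Extending the same adjustment to co-intervention use is tempting, but no gain has been calculated for it.

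**What to change.** In Statistical analysis, or in the analysis plan before unblinding, add for the Global Rating of Change:

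- a logistic model with arm, baseline worst pain (NRS) and baseline VISA-A;
- the standardised (marginal) relative risk, risk difference and number needed to treat from that model, each with a 95% confidence interval;
- the crude counts and unadjusted estimates alongside.

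Naming the two covariates in advance prevents a choice made after seeing the results. The cost is a sentence of text, a little more analysis code, and the possible 2-3% loss of precision if neither score is prognostic. No new data or participants are needed.

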## Discussion

Mid-portion AT is common and disabling and up to 40% of people with AT fail to respond to first-line conservative treatment [64]. Heel lifts have recently been found to be more effective than eccentric calf exercise (a guideline recommended treatment) in pain, disability and health-related quality of life outcome measures [14]. However, to our knowledge, there has been no trial comparing heel lifts to a sham [12, 14, 65]. Without the comparison to a sham intervention, it is unknown whether the efficacy of heel lifts is due to specific treatment effects, natural history or placebo. In addition, there are currently no Achilles tendinopathy-specific study investigating heel lifts and their suspected mechanism (i.e. changing biomechanical variables) [16].

The study protocol described here will overcome these limitations. We have included a sham intervention, and our biomechanical assessment is on a tendinopathy-specific cohort. At present, there are no empirically proven guidelines for the prescription of heel lifts (e.g. height or material). Considering this limitation, we chose heel lifts that are supported by the literature [14] and are commercially available to ensure our findings are generalisable to clinical practice. We have deliberately not included exercise, as it may confound the results by reducing symptoms of pain and disability instead of the heel lifts [66]. Instead, we will provide guideline and expert recommended education to both groups [7], which will overcome any ethical concerns of ‘withholding usual care’.

Outcomes from our clinical trial will provide much needed evidence regarding a common biomechanical intervention currently used to manage symptoms in people with mid-portion Achilles tendinopathy. This information will assist clinicians treating people with this condition and may be used in future clinical guidelines.

## Trial status

This is the first version of this protocol (20 July 2023). Advertising for participants commenced in July 2023 and is expected to conclude December 2024. The final results are expected to be available in August 2025 and disseminated via peer review publication and conference presentations.

